#### Secondary analyses

Secondary analyses will be conducted to examine if the primary outcome is mediated by the cognitive and affective variables. Following the approach by MacKinnon and others [81-87], we will conclude that cognitive or affective variables are potential mediators if they change the estimate of intervention effect once included in the model. To test for mediation effect, Statistical Model #1 will be used with MVPA (outcome measure) and with each of the potential mediators. We will refer to Models as Model #1a: MVPA (after 17 weeks) = MVPA (baseline) + study group + covariates; and Model #1b: Mediator variable (after 17 weeks) = Mediator variable (baseline) + study group + covariates. In addition to Models #1a and #1b, the following Statistical Model #2: will be fit: MVPA (after 17 weeks) = MVPA (baseline) + study group + mediator variable (after 17 weeks) + covariates. To explore mediation, we will use the “Causal Steps Method” [88] and evaluate significance of group in Models #1a and #1b, and mediator in Model #2. Effect sizes will be calculated using estimates for regression coefficients and standard errors. Percent of variation mediated will be determined [89].

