### Sample size determination and data analysis

#### Power calculations

Sample size calculations incorporated school-based research power approaches [65,66] and were informed by the work done in our pilot study and other studies using MVPA as a primary outcome [67,68]. We assumed a small effect size of 0.20 and an intraclass correlation coefficient (ICC) of 0.02, as noted from the Trial for Activity in Adolescent Girls [67]. Assuming a standard deviation of 80 for minutes of MVPA over 7 days [68], this effect size of 0.20 corresponds to a difference of 16 minutes/week between groups. Given that girls receiving the intervention are encouraged to accumulate at least 60 minutes/day of MVPA, this mean difference is reasonable to expect with a control group that consists of a number of girls who may have never been involved in any organized MVPA due to obstacles, such as limited free or low-cost programs [69]. Using this effect size and ICC, 24 schools (12 intervention) with 50 girls per school would provide power .80 and alpha = 0.05 for two-tailed comparison between two groups. To allow for 20% attrition (12 girls per school) [36,69-71], we plan to recruit 62 girls per school each year.

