#### Data analysis

Data will be analyzed using SAS 9.3 (SAS Institute Inc., Cary, NC) [72]. Outcome measures include the primary outcome: minutes of MVPA; secondary outcomes: CV fitness, BMI, and percent body fat; and mediating cognitive and affective variables. Potential covariates measured at baseline are personal factors and behaviors. To adjust for non-independence of observations within each school and the dependence within person, analyses below will be carried out using a multilevel model approach frequently used in group randomized trials [73] that will incorporate baseline measures as covariates [74,75]. Multilevel generalized linear models [73,76] will be fit for ordinal, and discrete outcomes using appropriate link functions. Assumptions of normality for continuous outcome variables will be evaluated; normalizing transformations or generalized linear mixed effect models will be used if warranted [76].

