#### Primary analyses

Primary analysis is of intention to treat type [78,79], which gives a conservative estimate of treatment effect compared with what would be expected if there was full compliance [80]. Effect sizes and their confidence intervals (adjusted for baseline values of outcomes and nested study design) will be computed. Variance components (school and participants) will be estimated.

We will use: Statistical Model #1: Outcome (after 17 weeks) = outcome (baseline) + study group + covariates. The essential parameter tested in this model is the coefficient for the study group variable. Covariates will be included if preliminary analyses reveal group differences at baseline despite randomization. We will model 9-month post-intervention F/U MVPA, controlling for MVPA after 17 weeks (immediately post-intervention): MVPA (9-month post-intervention F/U) = MVPA (after 17 weeks) + study group + covariates.

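### Mediation Model #2 leaves out the baseline mediator, so mediation can be declared where there is none, and the causal-steps rule makes any finding depend on a significant primary test

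*Protocol article*

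**What the plan says.** All the mediation models are in the protocol article under Secondary analyses.

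- Model #1a regresses 17-week MVPA on baseline MVPA, study group and covariates.
- Model #1b is "Mediator variable (after 17 weeks) = Mediator variable (baseline) + study group + covariates".
- Model #2 is "MVPA (after 17 weeks) = MVPA (baseline) + study group + mediator variable (after 17 weeks) + covariates".

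The same section gives two criteria. The first reads "we will conclude that cognitive or affective variables are potential mediators if they change the estimate of intervention effect once included in the model". The second is the causal-steps method, under which the investigators will "evaluate significance of group in Models #1a and #1b, and mediator in Model #2".

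The covariates term is described elsewhere. Data analysis says "Potential covariates measured at baseline are personal factors and behaviors", and Primary analyses says "Covariates will be included if preliminary analyses reveal group differences at baseline despite randomization". The cognitive and affective variables (benefits, barriers, enjoyment, social support, self-efficacy, motivation) have their own Measures subsection, separate from personal factors and behaviors.

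**The concern.** Group is randomised; the mediator is not. A girl who starts with high self-efficacy or enjoyment will tend to score high again at 17 weeks, which is why Model #1b adjusts for the starting value. If that starting value also relates to her 17-week activity beyond what her baseline MVPA captures, Model #2 credits the 17-week mediator with a relation that was there before the intervention. Theoretical underpinnings makes such a relation plausible, since it holds that these variables act on MVPA.

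The decision rule adds a second difficulty. Causal steps cannot declare mediation unless the total effect in Model #1a is significant, while the change-in-estimate criterion can name a potential mediator with no test at all. The two can disagree, and the section does not say which governs.

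Mediation is the stated secondary objective, and the Discussion expects the trial to help identify theoretical mediators and refine the components. An inert construct could be credited, or an active one overlooked.

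**Working it through.** **The plan's own figure.** The article gives no power or error rate for the mediation analysis. The nearest figure is the planned power of 0.80 for the primary comparison, based on "We assumed a small effect size of 0.20 and an intraclass correlation coefficient (ICC) of 0.02" with 24 schools (12 per arm) and 50 girls per school. I take 0.80 as given; whether it follows from its inputs is a separate question.

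**Size of the confounding.** Let M0 and M1 be the mediator at baseline and 17 weeks, Y0 and Y1 MVPA at the same times, all in SD units, with no true mediator effect (b = 0) and a residual effect d of M0 on Y1:

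Y1 = 0.5·Y0 + 0.20·group + 0·M1 + d·M0 + school + error

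Assumed, not in the document: correlation 0.6 between M0 and M1, 0.5 between Y0 and Y1 when d = 0, 0.3 between M0 and Y0, and an intervention effect on the mediator of a = 0.3. From the document: 24 × 50 girls, ICC 0.02, group effect 0.20 SD.

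With M0 left out, the expected coefficient on M1 is

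d × 0.6(1 − 0.3²) / (1 − 0.6² × 0.3²) = d × 0.546 / 0.9676 = 0.564·d

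For d = 0.05, 0.10 and 0.20 this gives 0.028, 0.056 and 0.113; the true value is zero. With "Assuming a standard deviation of 80 for minutes of MVPA over 7 days", these d values mean 4, 8 and 16 minutes/week per SD of the baseline mediator (80 × d).

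**False declarations.** 1,500 simulated trials per row; group tested on adjusted school means (t, 22 df), mediator tested with school-clustered standard errors.

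| d | Mean M1 coefficient, as written | Mediator significant, as written | All causal steps pass, as written | Mediator significant, M0 added | All causal steps pass, M0 added |
|---|---|---|---|---|---|
| 0 | 0.000 | 4.9% | 3.9% | 6.2% | 4.8% |
| 0.05 | 0.028 | 17% | 12% | 5.4% | 3.6% |
| 0.10 | 0.057 | 57% | 39% | 5.0% | 3.3% |
| 0.20 | 0.114 | 99% | 67% | 5.6% | 3.9% |

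The simulation error of a rate near 5% is √(0.05 × 0.95 / 1500) = 0.6 percentage points.

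**Change in estimate.** At d = 0.10 the mean group estimate moves from 0.199 (Model #1a) to 0.181 (Model #2), a fall of (0.199 − 0.181) / 0.199 = 9% with no mediation present. The first criterion gives no threshold by which to judge such a shift.

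**The Model #1a condition.** The probability that all three tests pass cannot exceed the probability that Model #1a passes. At the planned 0.80, causal steps therefore cannot declare mediation in at least 20% of trials even if the full 16 minutes/week is real. Simulating true mediation with a = 0.3 and d = 0:

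| b | Direct effect | Total effect (direct + a × b) | #1a significant | Causal steps declare | #1b and #2 both significant |
|---|---|---|---|---|---|
| 0.2 | 0 | 0.06 | 10% | 10% | 97% |
| 0.3 | 0 | 0.09 | 18% | 18% | 97% |
| 0.2 | 0.14 | 0.20 | 68% | 67% | 97% |

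The first two rows have total effects below half the planned 0.20 SD, so their low rates are not a forecast for this trial. The 68% reflects a simulation in which baseline MVPA does not reduce the between-school variance; it is not a recalculation of the planned power.

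**Error-prone scale.** Suppose instead that a stable trait accounts for 60% of the variance of each measure, the mediator and MVPA traits correlate at 0.4, and b = 0. The mediator is then significant in 98% of trials as written and 55% with M0 added; the coefficient falls from 0.101 to 0.064.

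**The case against.** Data analysis also says the models will take in baseline measures as covariates, so the baseline mediator may have been intended. But each displayed equation carries only the earlier value of its own outcome, covariates are identified as personal factors and behaviors, and they enter only on baseline imbalance between groups. If the term was intended, Model #2 should show it.

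Model #2 already contains baseline MVPA, so only a residual relation does harm. That stands. The document gives no value for it, and with none the error rate is nominal. A reader might infer that false mediation will occur, or attach one fixed percentage to it; neither is supported.

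Requiring group to be significant in Model #1b and the mediator in Model #2 does examine both paths. That also stands, so it would be wrong to infer that the indirect effect goes unaddressed. The added Model #1a condition is conservative and arguably natural when the question is what mediates a change in MVPA. It follows that real mediation may be missed, not that it will be.

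The first criterion can be read as defining a potential mediator, with the three tests as the operational rule. That is possible, but the article does not say so. An interval method for the indirect effect may properly sit in an analysis plan that is not shown; its absence is not the point. The point is the rule the article does fix.

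A reader might also infer that measuring mediator and MVPA together at 17 weeks is an error that calls for a 9-month model. The stated question concerns the primary outcome, which is set at 17 weeks. A 9-month model answers a different question, and choosing it is a preference.

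**Conclusion.** The concern holds in two parts.

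First, Model #2 omits a baseline variable that is already collected and already used in Model #1b. Its mediator coefficient is therefore open to confounding, and mediation can be declared where none exists. How often depends on an unknown: from the nominal 5% when there is no residual relation to nearly every trial at 0.20 SD, under the assumed correlations.

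Second, the causal-steps rule may miss real mediation whenever Model #1a is not significant, and it stands beside a criterion without a test and with no statement of which prevails.

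The omission can be read directly from the equations; the magnitudes are illustrations that rest on assumed paths. This is an exploratory secondary objective, and the primary efficacy test is not touched. The change should be made, but it does not bear on the trial's main conclusion.

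**What to change.** 1. Write Model #2 with the baseline mediator added: 17-week MVPA on baseline MVPA, baseline mediator, study group, 17-week mediator and covariates.
2. Replace both criteria with one rule: test the indirect effect (group coefficient in Model #1b times mediator coefficient in Model #2) with a 95% confidence interval that respects clustering, for example a Monte Carlo interval or a bootstrap that resamples schools. Report it whether or not Model #1a is significant.
3. State that the added term reduces confounding by the baseline mediator but may not remove it when the scale is measured with error.

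The cost is a change of wording and a little programming. Every variable is already collected, and neither the sample size nor the primary analysis changes.

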The project’s measurement coordinator trains staff according to standardized protocols and certifies each one for data collection only after successful practice demonstrations. The measurement coordinator or project manager oversees all sessions to ensure fidelity to the measurement protocol. The same group of trained staff collects data for each cohort or matched pair including an intervention and control school over the same three- or four-week period. Only half of the data is collected from half of the girls at each paired school during the first week. The remainder of the data is collected from the same wave of girls during either the second or third week. Half of the data is obtained from the other half or wave of girls at each school during the second or third week with the remaining half of the data being collected during the following week (week three or four, respectively). Whether the data collection spans across three or four weeks for each pair of schools is determined based on requests from school administrators. To reduce the potential of non-typical PA occurring during a single week for all girls at a particular school site, two waves are used during all data collection periods in every participating school. Obtaining half of the data, as opposed to all, at a single time point also reduces the response burden for the girls and decreases the time needed during a school day. Complete data are collected at pre-intervention/baseline and immediately post-intervention (after 17 weeks). At 9-month post-intervention F/U, only PA is measured (via accelerometer) to assess for any long-term effects. For completing the survey data at each time period, girls receive an incentive, such as a T-shirt or a drawstring backpack, with the Girls on the Move logo. For wearing the accelerometer as instructed for one week at each time period, girls receive a $20.00 gift card to a local general store. If the data are inadequate due to limited wear-time and the accelerometer needs to be re-worn, girls receive a reduced gift card amount of $10.00 after the second week of wearing it.

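### Model #2 omits the baseline mediator that Model #1b includes, so its mediator slope can carry pre-existing differences between girls and inflate false findings of mediation

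*Protocol article*

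**What the plan says.** Under Secondary analyses, the protocol article sets out the mediation models as equations. The path from group to mediator (Model #1b) is "Mediator variable (after 17 weeks) = Mediator variable (baseline) + study group + covariates". The path from mediator to activity (Model #2) is "MVPA (after 17 weeks) = MVPA (baseline) + study group + mediator variable (after 17 weeks) + covariates". Only the first contains the baseline mediator.

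The decision uses the causal-steps method: the team will "evaluate significance of group in Models #1a and #1b, and mediator in Model #2". The same section also calls variables potential mediators "if they change the estimate of intervention effect once included in the model".

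On covariates, the Data analysis section states "Potential covariates measured at baseline are personal factors and behaviors", and lists the cognitive and affective variables separately, among the outcome measures. The Primary analyses section adds "Covariates will be included if preliminary analyses reveal group differences at baseline despite randomization". A general sentence under Data analysis says that the multilevel approach "will incorporate baseline measures as covariates".

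**The concern.** Randomization protects the group comparisons in Models #1a and #1b. It does not protect the mediator slope in Model #2, which compares girls with one another within arms. A girl who already enjoyed activity, or already felt able to do it, will tend to score high at 17 weeks and also to be more active, whether or not the mediator changes behavior.

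The protocol's own theory section expects such links: it holds that personal characteristics and past behavior shape these variables, and that the variables in turn affect MVPA. Baseline MVPA is in Model #2 and blocks part of the path. But it may rest on as few as four days of accelerometer data (Measures, Outcomes), so it records usual activity imperfectly.

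At stake is the stated secondary objective, and with it the aim in the Discussion of identifying the theoretical mediators that matter. A variable that the intervention shifts, but that does nothing to MVPA, could be credited with the effect.

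**Working it through.** **Inputs from the article.** 24 schools, 50 girls per school, ICC 0.02, group effect on MVPA 0.20 SD (Power calculations), and the three-step rule. The article states no power or error rate for mediation, so there is no figure to reproduce.

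**Assumed inputs.** Mediator stability s (baseline to 17 weeks), reliability of MVPA, the mediator–activity correlation and the size of the group effect on the mediator. The article gives none of these, so ranges are shown. The true effect of the 17-week mediator on MVPA is zero throughout.

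**Slope by hand, stable-trait model.** Let r be the correlation of mediator with MVPA and p the correlation of baseline with 17-week MVPA, within arm and standardized.
- Slope as written: r(1 − p) / (1 − r²)
- Slope with the baseline mediator: r(1 − p) / [(1 − r²) + (s − r²)]

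Take trait correlation 0.3, s = 0.7, p = 0.5. Then r = 0.3 × √(0.7 × 0.5) = 0.1775, r² = 0.0315 and r(1 − p) = 0.0887.
- As written: 0.0887 / 0.9685 = 0.092
- With the baseline mediator: 0.0887 / (0.9685 + 0.6685) = 0.054

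The true value is zero, so the added term removes part of the bias here.

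**Slope by hand, link only through the baseline mediator.** Take reliability 0.5, correlation of baseline mediator with usual activity 0.3, stability 0.6. The 17-week mediator then correlates 0.6 × 0.3 × √0.5 = 0.127 with MVPA.
- As written: (0.127 − 0.5 × 0.127) / (1 − 0.127²) = 0.065 (simulated mean 0.064)
- With the baseline mediator: 0 (simulated −0.001)

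**Full three-step rule by simulation.** 1,500 trials per setting, random-intercept GLS, 22 degrees of freedom for group. Where the link runs through the baseline mediator, with a group effect of 0.20 on the mediator and 0.20 SD on MVPA, false declarations are:

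| Reliability | Correlation | Stability | Model #2 as written | Baseline mediator added |
|---|---|---|---|---|
| 0.5 | 0.1 | 0.5 | 6.3% | 2.9% |
| 0.7 | 0.2 | 0.5 | 14.7% | 2.7% |
| 0.5 | 0.2 | 0.5 | 16.3% | 2.9% |
| 0.5 | 0.3 | 0.6 | 43.7% | 3.1% |
| 0.6 | 0.4 | 0.6 | 56.3% | 2.9% |
| 0.5, and baseline mediator has its own effect of 0.1 on later MVPA | 0.3 | 0.6 | 58.7% | 3.1% |

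Check on the fourth row: both group steps are met in 60.5% of trials and the mediator step in 72.5%; 0.605 × 0.725 = 0.439, close to 43.7%. The apparent share mediated in that row is about 6%.

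Under the stable-trait model (mediator shift 0.3 SD, 0.20 SD on MVPA), false declarations at trait correlation 0.3 are about 70% as written and 24% with the term added. For trait correlations 0.2 to 0.4 they are about 50% to 76% and 14% to 44%.

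**Where the excess disappears** (as written vs term added):
- correlation zero: 3.0% vs 3.2%
- stability zero: 2.7% vs 2.6%
- reliability of MVPA 0.99: 4.9% vs 4.3%
- no group effect on MVPA: about 7% vs 3% in the stable-trait model, and 3.7% as written in the other
- no group effect on the mediator: 3.6% as written

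**What the added term does not reach.** With an unmeasured common cause arising after baseline (loading 0.3), false declarations are 60.3% as written and still 43.2% with the term.

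**Precision.** In the stable-trait base case with n = 1,200:
- As written: residual variance 1 − 0.25 − 0.092 × 0.0887 = 0.742, so SE = √[0.742 / (1,200 × 0.9685)] = 0.025.
- With the term: mediator variance left is 0.9685 − 0.6685² / 0.9685 = 0.507; residual variance 0.75 − 2 × 0.054 × 0.0887 = 0.740; SE = √[0.740 / (1,200 × 0.507)] = 0.035.

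The slope's variance rises by a factor of 0.9685 / 0.507 = 1.9.

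**The case against.** The best reply is the general sentence that the analyses will incorporate baseline measures, together with the listing of mediators among the outcomes. On that reading, the covariates term in Model #2 might already hold the baseline mediator, and a condensed article need not spell it out. The rule that admits covariates on group imbalance is also stated under Model #1. This leaves room for the sponsor to have meant the right thing. But the equations say which baseline score goes where, and Model #2 names baseline MVPA only. Covariates are defined as a class that does not include the mediators. An imbalance rule is also beside the point for confounding within arms. If the term is intended, the equation still needs correcting.

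It is also fair that the analysis is secondary and worded as exploratory, and that the sizes rest on assumed inputs. Both stand.

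Three stronger readings are tempting and are not supported:
- **That the two paths measure different things, change in Model #1b and level in Model #2.** Model #1b has the 17-week level as its outcome. Under randomization, its group coefficient targets the difference in that level with or without the baseline score. The fault is confounding of the Model #2 slope, not a mismatch of quantities.
- **That an inert variable will usually be declared a mediator.** In the stable-trait base case the mediator is significant in Model #2 in 94.5% of trials (35% with the baseline term), but that is one step of three. The full rule gives about 70%, and other plausible settings give far less.
- **That the added term cures the problem.** The working shows that it does so only when the link runs through the measured baseline mediator.

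**Conclusion.** The point holds. Model #2 as written lacks the baseline mediator, nothing else in the article clearly supplies it, and the mediator slope is left open to stable differences between girls. False declarations of mediation under the full rule rise to between about 6% and 59%, or 50% and 76%, depending on how the pre-existing link arises. The comparable figures with the term are about 3%, or 14% to 44%.

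These sizes depend on a mediator that is stable over 17 weeks, related to usual activity, and not fully accounted for by measured baseline MVPA. They also depend on an intervention that moves both the mediator and MVPA. The protocol's theory and its short accelerometer record make the first set of conditions plausible, but the article quantifies none of them.

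The change-in-estimate criterion is exposed through the same slope. The primary analysis and the comparisons of secondary outcomes between groups are unaffected. This is a worthwhile correction to a secondary analysis, not a threat to the trial's main result.

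**What to change.** Write Model #2 as: MVPA (after 17 weeks) = MVPA (baseline) + study group + mediator (after 17 weeks) + mediator (baseline) + covariates. State beside it that this removes only part of the mediator–outcome confounding, so that a significant mediator is not read as proof of a causal path.

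No new data are needed: "Complete data are collected at pre-intervention/baseline and immediately post-intervention (after 17 weeks"). The cost is one term per model and some precision. The slope's standard error rises by roughly 1/√(1 − s²), which is 1.25 at stability 0.6 and 1.40 at 0.7, where its variance nearly doubles. Some power to detect true mediators is therefore lost, and the plan should say so.

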### Aims and hypotheses

The main study aim is to evaluate the efficacy of our comprehensive 17-week school-based intervention in increasing girls’ minutes of MVPA and improving CV fitness, BMI, and percent body fat immediately post-intervention (after 17 weeks) and at 9-month post-intervention follow-up (F/U; 9 months after end of intervention). The primary outcome is minutes of MVPA measured after 17 weeks. The intervention includes three components, two of which are individual-level: 1) two face-to-face motivational, individually tailored counseling sessions with a registered nurse, and 2) an interactive Internet-based session during which each girl receives individually tailored motivational and feedback messages (11 weeks). One group-level component, a PA club led by PA instructors (e.g., individuals from community who have experience conducting youth physical activity programs; teachers, including physical education; and sports team coaches), provides an important venue after school to assist girls in establishing a behavioral pattern of MVPA. Girls receiving the intervention will be compared to those in control schools having usual school offerings, some of which may include physical education.

Specific hypotheses include:

•Immediately post-intervention, minutes of MVPA (measured by accelerometer) will be greater by 16 minutes/week among girls in intervention, as compared to control, schools.

•At 9-month post-intervention F/U, minutes of MVPA will be greater among girls in the intervention than control schools.

•Immediately post-intervention and at 9-month post-intervention F/U, CV fitness will be higher and BMI and percent body fat will be significantly lower among girls in the intervention than control schools.

A secondary objective is to examine if MVPA changes are mediated by cognitive (e.g., perceived benefits of PA, barriers to PA, PA self-efficacy, social support) and affective variables (e.g., enjoyment of and motivation for PA).

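### Two rules for mediation are given without saying which decides, and one of them, causal steps, makes every mediator finding depend on a significant total effect that an indirect effect does not need

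*Protocol article*

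**What the plan says.** Under Aims and hypotheses the article states: "A secondary objective is to examine if MVPA changes are mediated by cognitive" and affective variables. The Secondary analyses section then gives two criteria.

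- **Change in estimate.** A variable is taken to be a potential mediator if the intervention estimate changes once the variable enters the model. No size of change and no test is attached.
- **Causal steps.** The named method is the Causal Steps Method, and the plan is to "evaluate significance of group in Models #1a and #1b, and mediator in Model #2". The total-effect model is "Model #1a: MVPA (after 17 weeks) = MVPA (baseline) + study group + covariates". Model #1b puts the mediator in the place of MVPA. Model #2 adds the 17-week mediator to #1a.

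The section also plans effect sizes from coefficients and standard errors, and a percent mediated. It does not rank the two criteria.

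The group test in #1a is the trial's primary comparison. Under Power calculations the design is said to be such that "24 schools (12 intervention) with 50 girls per school would provide power .80 and alpha = 0.05 for two-tailed comparison between two groups".

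**The concern.** An indirect effect is the product of two paths: group to mediator (#1b) and mediator to MVPA given group (#2). Showing that this product is not zero does not require a significant total effect. The total effect is the sum of the indirect and direct effects. It can miss significance because the trial is short of power for it, or because a direct effect runs the other way, while both mediator paths are clear.

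Causal steps includes the test of the total effect. All candidates (benefits, barriers, two self-efficacy measures, enjoyment, social support, motivation) share the same #1a result, so one non-significant primary test removes them all together. That is also when the sponsor most needs to know whether the targeted variables moved and whether they matter for MVPA. The Discussion section names identifying theoretical mediators as one of the trial's uses.

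With two unranked criteria, the same data could be reported as showing mediation under one and not under the other.

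**Working it through.** **Inputs from Power calculations.** "We assumed a small effect size of 0.20 and an intraclass correlation coefficient (ICC) of 0.02"; "Assuming a standard deviation of 80 for minutes of MVPA over 7 days"; "this effect size of 0.20 corresponds to a difference of 16 minutes/week between groups"; 12 schools per arm with 50 girls each (600 per arm); two-sided alpha 0.05. The half-size effect (d = 0.10, 8 minutes/week) is our scenario.

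**1. The plan's own power for the #1a test.**
- Design effect = 1 + 49 × 0.02 = 1.98.
- SE of the standardised difference = √(2 × 1.98/600) = 0.0812.
- d/SE = 0.20/0.0812 = 2.46.
- Power = Φ(2.46 − 1.96) = 0.692 (normal), or 0.653 with a t reference on 22 df (24 schools − 2).

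The stated .80 is therefore not reproduced without baseline adjustment. With an assumed baseline–outcome correlation of 0.5 at both levels it comes near: 0.811 (normal) or 0.775 (t). That discrepancy is a separate matter, so results are shown on both footings.

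**2. Chance that #1a is not significant.**

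| Basis | d = 0.20 | d = 0.10 |
|---|---|---|
| Stated power .80 accepted | 20% | about 71% |
| Stated inputs, no baseline adjustment (normal; t) | 30.8%; 34.7% | 76.7%; 78.2% |
| Correlation 0.3, both levels (normal; t) | 27%; 31% | 75%; 77% |
| Correlation 0.7, both levels (normal; t) | 7%; 9% | 59%; 62% |

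- First row: power .80 implies d/SE = 1.96 + 0.84 = 2.80. Half of that is 1.40, and Φ(1.40 − 1.96) = 0.29.
- Adjusted rows: d/SE is divided by √(1 − r²). For r = 0.7 this gives 2.46/0.714 = 3.45, and Φ(3.45 − 1.96) = 0.93.
- If adjustment reduces only the within-school variance, the t-based figures for r from 0.3 to 0.7 are 33% to 23%, and 77% to 73%.
- The article gives no baseline–outcome correlation, so the range cannot be narrowed.

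**3. Net loss against testing #1b and #2 jointly.** Step 2 counts only failures at #1a. The rest depends on mediator paths that the article does not give. Cluster simulations used 24 × 50 girls, ICC 0.02 for mediator and MVPA, and no baseline adjustment.

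| Total effect | Assumed mediator shift (SD) | Assumed slope | All three tests | #1b and #2 only |
|---|---|---|---|---|
| 0.20 | 0.4 | 0.25 | about 67% | 99.9% |
| 0.20 | 0.2 | 0.25 | about 46% | 66% |
| 0.10 | 0.4 | 0.25 | about 21% | 99.8% |
| 0.10 | 0.3 | 0.30 | about 21% | 94% |

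Repeat runs move these by a point or two. In the first two rows the indirect effects are 0.4 × 0.25 × 80 = 8 and 0.2 × 0.25 × 80 = 4 minutes/week.

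**4. Is the #1a condition needed to control false positives?** In simulation the joint test of #1b and #2 was falsely positive in about 4–5% of trials when one path was zero and 0.3% when both were. It holds the nominal level without #1a.

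**The case against.** A reader might infer that the plan forbids calling anything a mediator unless the total effect is significant, and that a true mediator is therefore missed in about a third of trials at the planned effect and about 80% at half of it. The article does not support this, for four reasons.

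- The gate is not written out. It comes from the method named. The change-in-estimate rule in the same section has no such gate.
- The third and the 80% apply to an analysis without baseline MVPA, whereas Model #1a includes it. They also imply power of about 0.65–0.69 rather than the stated .80.
- The #1a test need not be by far the weakest of the three. With a 0.2 SD mediator shift, the joint test succeeds about as often (66%) as #1a does at the planned effect (0.653 to 0.692). The near-certain detection needs a 0.4 SD shift, twice the planned MVPA effect.
- The mediation objective is not switched off by a null primary result. Nothing makes fitting #1b and #2, or reporting effect sizes, conditional on #1a.

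It can also be said that this is an exploratory secondary objective in a condensed article, that causal steps is a recognised conservative method, and that interval methods are often left to the SAP. The first two limit the severity. The last does not answer the point: the article names the method and its tests, so this is a rule it has fixed and not a detail left open. In every setting tried, causal steps found the mediator less often than the joint test.

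**Conclusion.** The point holds as a modest one. The plan sets out two mediation criteria and does not say which governs. The only one with a test carries a condition that is not needed to show an indirect effect and can remove every candidate mediator together.

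The chance that the condition fails at the planned effect is between about 7% and 35%, depending on baseline adjustment, and 20% on the plan's own power. At half the planned effect it is 59–78%, and about 71% on the plan's own power. The adjusted figures rest on assumed correlations of 0.3 to 0.7. The net loss rests on assumed mediator paths: at the planned effect without adjustment it is about 33 percentage points with a 0.4 SD shift (99.9 − 67) and about 20 with a 0.2 SD shift (66 − 46). The primary analysis is unaffected.

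**What to change.** In Secondary analyses, remove significance of group in Model #1a as a condition for mediation and name one deciding criterion. For each mediator this would be the indirect effect in minutes/week, that is, the group coefficient in #1b times the mediator coefficient in #2, with a 95% confidence interval that respects school clustering (from cluster resampling or a Monte Carlo interval). Report it whatever the primary result, and keep percent mediated as description only. This also replaces the change-in-estimate rule, because the indirect effect puts a size and an interval on that change.

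The cost is a sentence or two in the plan and some computing, with no new data. The downside is that an indirect effect may appear beside a non-significant total effect. It must then be worded as evidence about a pathway and not as evidence that the intervention raised MVPA overall.
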